#### Plans to give access to the full protocol, participant-level data, and statistical code {31c}

The SMILES protocol is publicly available on clinicaltrials.gov. There are no current plans for granting public access to the participant-level dataset and statistical code.

### Oversight and monitoring

#### Composition of the coordinating centre and trial steering committee {5d}

The Trial Steering Committee responsibilities, in consultation with site PIs, include governance, protocol development and amendments, study design, planning, monitoring, and progress along with data collection and validation, and preparation of the manuscript for publication. No publications will be disseminated without the Trial Steering Committee’s prior approval. PIs at each participating site will be responsible for study conduct and day-to-day operations. The Trial Steering Committee consists of project coordinators, data managers, and research assistants (i.e. postdoctoral fellow, PhD and MSc students) and is led by the coordinating centre PI. Data analyses will be performed by the study statistician and a member of the Trial Steering Committee. A member of the Trial Steering Committee will meet bi-weekly with the participating site PIs. The Trial Steering Committee will meet once a month to discuss study progress.

#### Composition of the data monitoring committee, its role and reporting structure {21a}

This study has an external data monitoring committee (E-DMC). According to the DMC Charter, the DMC will be responsible for ongoing monitoring of participants’ efficacy and safety in the study. The recommendations made by the DMC to alter the conduct of the research will be forwarded to the Sponsor for a final decision. The Sponsor will forward such decisions to regulatory authorities, as appropriate. If the DMC recommendation is to halt the trial due to any other serious toxicity, then a substantial amendment must be submitted and approved by the MHRA before re-initiating recruitment. The DMC will be independent of the study team and will have no direct involvement in other trial aspects. The DMC will develop operation procedures in consultation with the sponsor, documented in the DMC charter.

#### Adverse event reporting and harms {22}

We will closely monitor participants for known potential and unexpected adverse events. The research coordinator will contact families during the first 1–2 weeks to determine any adverse events, especially behavioural, and then contact them again at 4 and 8 weeks by telephone. They will also be encouraged to contact the investigators or their local paediatricians/haematologists if they experience unexpected events. The number of children with treatment-related adverse events from montelukast will be measured by looking at all adverse events, including days of illness and days lost from preschool/school. Hospital admissions for pain, acute chest syndrome, stroke, planned surgery, splenectomy, and gallstones are expected in patients with SCA. These admissions will not be reported in this trial unless the CI believes that there is a causal relationship between the drug and the event. The management of any symptoms or exacerbations will be per usual clinical practice. The local PI or delegated research staff will discuss specific issues with families throughout the study. Any concerns which cannot be satisfied at a local level will be forwarded to the CI.

Adverse events will be recorded on case report forms by the study coordinator and encrypted and stored separately from other data collected. If the CI considers it necessary to know whether a participant is assigned to montelukast or placebo to manage a specific serious adverse event, the treatment may be unblinded for that participant. The GOSH pharmacy will access the randomisation schedule if required and supply the needed information to unblind the participant. The most frequently occurring adverse experiences consistent with the safety profile of montelukast include abdominal pain, somnolence, thirst, headache, vomiting, and psychomotor hyperactivity. If the participant is withdrawn due to an adverse event, we will arrange for follow-up visits or telephone calls until the adverse event has resolved or stabilised.

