### Assignment of interventions: blinding

#### Who will be blinded {17a}

The CI, local PIs, and researchers involved in data collection will be blind to group allocation. Pharmacists will be unblinded for dispensing purposes. Statisticians will be unblinded to allocation before preparation of the participant flow diagram and outcome analysis.

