### Data collection and management

#### Plans for assessment and collection of outcomes {18a}

At baseline, caregivers will complete measures of demographics (e.g. age, gender, ethnicity, parental education), pain burden, asthma symptoms, family functioning, child executive function, and sleep questionnaires. A clinical psychologist ([name]; first author) with significant assessment experience will train PhD candidates and paediatric neuropsychology MSc students to conduct the cognitive evaluation and assist caregivers with questionnaires. Assessors will administer cognitive testing to patients on a tablet computer. Given that proximity to a blood transfusion has been shown to influence cognition [20], we will test patients at the same time in their transfusion cycle at baseline and post-treatment (e.g. if we test a patient in the week before a transfusion at baseline, we will test a patient in the week before a transfusion at post-treatment).

Questionnaires and testing should take about 1 h to complete. If a family agrees (optional assessments), patients will undergo brain MRI after cognitive testing, and the research team will organise a reading of overnight oximetry. Patients will then be randomised to the control or treatment arm by the GOSH pharmacist. Montelukast will be immediately dispensed or posted to families. At the 12-week follow-up, caregivers and patients will complete questionnaires and cognitive testing again. Optional assessments will also be completed (see Fig. 1) Patients and families will complete an adverse event assessment and visit the GOSH pharmacy for montelukast accountability. We will compensate families for transportation (e.g. taxis) to and from the site for both visits. The study coordinator will call families at weeks 2, 6, and 14 to check for any adverse events (e.g. hospitalisations), focusing on potential patient behaviour changes (see Table 2) and medication adherence.

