#### Interim analyses {21b}

Interim analyses are not planned as unexpected serious adverse events related to the intervention are not expected. The trial participation for each patient is short, and they will be followed up in their local paediatric haematology centres.

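### As worded, admissions for stroke, acute chest syndrome, pain and other listed causes go unreported unless a normally blinded investigator blames the drug; the text should limit this to expedited reporting and require counts by arm

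*Protocol article*

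**What the plan says.** All references are to the protocol article.

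- **Adverse event reporting and harms {22}** names the exempted events: "Hospital admissions for pain, acute chest syndrome, stroke, planned surgery, splenectomy, and gallstones are expected in patients with SCA". The next sentence sets the rule: "These admissions will not be reported in this trial unless the CI believes that there is a causal relationship" with the drug.
- **The same section**, two sentences before that rule, says the number of children with treatment-related adverse events "will be measured by looking at all adverse events, including days of illness and days lost from preschool/school". Later it has the study coordinator enter adverse events on case report forms.
- **Who will be blinded {17a}**: "The CI, local PIs, and researchers involved in data collection will be blind to group allocation". The section on unblinding {17b} lets the chief investigator (CI) learn one participant's allocation when that is needed to manage a specific serious adverse event.
- **Plans for assessment and collection of outcomes {18a}**: the coordinator telephones families at weeks 2, 6 and 14 "to check for any adverse events (e.g. hospitalisations", among other things.
- **Composition of the data monitoring committee {21a}**: the committee (DMC) is "responsible for ongoing monitoring of participants’ efficacy and safety in the study".
- **Interim analyses {21b}**: "Interim analyses are not planned as unexpected serious adverse events related to the intervention are not expected".

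**The concern.** The exemption turns on a causality judgement made one case at a time. That is a usual basis for deciding which events need urgent notification. It does not show whether a drug changes how often an expected event happens. For stroke, chest syndrome or a pain crisis in a child with sickle cell anaemia, the disease is always a sufficient explanation, so a blinded assessor will rarely have grounds to attribute a single case to the drug. A difference in rate appears only when all cases are counted in each arm.

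The document itself gives reasons to want those counts. The background section links airway obstruction and low oxygen saturation, which the treatment is meant to improve, to stroke risk. The objectives include respiratory and pain symptoms. The discussion hopes the data will bear on emergency healthcare use. Section {22} also names abdominal pain among the commonest adverse experiences on montelukast while exempting pain and gallstone admissions, where drug and disease are hard to tell apart. An unreported difference could therefore be a harm or a benefit.

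**Working it through.** The plan gives no figure on this point and no admission rate, so there is nothing to reproduce. The check sets the statements side by side.

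1. **Scope of the exemption.** It covers six kinds of admission: stroke, acute chest syndrome, pain, gallstones, splenectomy and planned surgery. It is stated to hold within the trial as a whole. Nothing confines it to expedited notification, and no other section brings these admissions back for DMC listings or the final report.

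2. **Who lifts it.** Only the CI's belief in a causal link does. The CI is blind except for individual emergency unblinding, which exists for clinical management and not for comparing arms.

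3. **What the rule does to a comparison by arm.** Let the true numbers of these admissions be A on montelukast and B on placebo, and let p be the share that the CI attributes to the drug. If attribution does not depend on arm, as blinding intends, the expected reported numbers are pA and pB. Blinding prevents bias in p, but it does not restore the lost events: reported counts shrink in both arms and approach zero as p does, whatever the ratio of A to B. The document gives no value for p. Labelling the events as expected suggests it would be small.

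4. **Against the rest of {22}.** The section undertakes to look at all adverse events and then withholds some of the most serious ones from reporting. Both can stand only if *reported* means something narrower than *recorded* or *tabulated*, and the section does not define it.

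5. **Against {18a}.** Families are asked about hospitalisations whatever the cause. The information is sought in both arms, and the text then says that part of it will not be reported. The weeks also differ: {18a} and Table 2 place the calls at 2, 6 and 14, while {22} places contacts in the first one to two weeks and at 4 and 8.

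6. **Against {21a}.** A committee charged with ongoing safety monitoring would, on the literal rule, not receive unattributed strokes or chest syndrome admissions.

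7. **Against {21b}.** The reason given for having no interim analysis concerns unexpected events related to the drug. It does not address a shift in the rate of expected ones, so it cannot justify leaving them out of safety monitoring.

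**The case against.** The strongest reply is that {22} uses two verbs. Adverse events are *recorded* on case report forms; the listed admissions are not *reported*. In a paragraph about expectedness and causality, the second verb may well mean expedited safety reporting, where such an exemption is ordinary. The calls ask about hospitalisations, and the auditing section names hospital records as source documents, so the events are probably retrievable in both arms. This stands, and it limits the point: the document does not show that the data will be missing. It also does not say that the narrow meaning is intended, and a site following the sentence literally would leave out an unattributed stroke.

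A second reply is that pain and respiratory effects are measured in other ways: the PedsQL pain dimensions, the C-ACT, overnight oximetry where feasible, and FLAIR imaging in the MRI subset. That is true, and it rules out saying that any such effect would be invisible. None of these counts admissions or strokes by arm.

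A third is that blind causality assessment is good practice. It is, and blinding is not the fault here. The fault is using attribution as the condition for reporting at all.

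Two stronger readings are tempting and are not supported:

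- A reader might infer that neither the DMC nor the final report *can* compare these admissions by arm. The calls and case report forms leave that open.
- A reader might infer from the word *efficacy* in the DMC remit that repeated unadjusted looks will inflate the type I error. No section gives a number of looks, a significance threshold or an efficacy stopping rule. The only halt described is for toxicity, and operating procedures are left to a charter that is not shown. What remains is a wording mismatch with {21b}.

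**Conclusion.** The point holds as a fault of wording with a safety consequence. The exemption in {22} is broader than it needs to be, has no stated limit, and disagrees with the all-adverse-events sentence in its own section, with the hospitalisation checks in {18a} and with the DMC's safety remit in {21a}. Followed literally, it keeps unattributed admissions in six categories, stroke and acute chest syndrome among them, out of any comparison by arm. If only expedited reporting was meant, the plan is sound in intent and needs one clarifying sentence.

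The size cannot be given in numbers, because the document states neither an admission rate nor how often the CI would attribute an admission to the drug. The conclusion rests on the plain wording of the rule and on the fact that a change in the rate of an expected event shows only in counts by arm. It should be corrected. The DMC efficacy wording is minor.

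**What to change.** In **Adverse event reporting and harms {22}**:

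- state that the exemption for expected admissions applies to expedited reporting only;
- state that every hospital admission is entered on the case report form with its date and cause, whatever the view on causality;
- state that these admissions are tabulated by arm for the DMC and in the final report;
- reconcile the contact weeks with {18a} and Table 2, so that it is clear when families are asked.

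As a minor wording change, reconcile the efficacy part of the DMC remit in {21a} with the absence of planned interim analyses in {21b}: either limit the remit to safety and trial conduct, or say what efficacy monitoring means and refer to the charter.

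The cost is small: one case report form line per admission, for information the calls already seek; one safety table; and a few words in the protocol and charter. Admissions that have already occurred can be recovered from hospital records. Sample size, visits and the primary analysis are unaffected.

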#### Frequency and plans for auditing trial conduct {23}

The Sponsor (UCL) is responsible for implementing quality control and quality assurance. A trial-specific monitoring plan will monitor the trial with the agreed plan. Initiation visits will be performed at each trial site before recruitment, followed by routine monitoring visits throughout the clinical trial. There will be study close-out visits once all data has been cleaned and queries have been resolved. We will submit protocol deviations that compromise safe drug administration or determine study endpoints to GOSH NHS Trust R&D Department. Protocol deviations will be included in the annual protocol review for the ethics committee. Source documents are original documents, data, and records from which participants’ CRF data are obtained. These include, but are not limited to, hospital records (from which medical history and previous and concurrent medication may be summarised into the CRF), clinical and office charts, laboratory and pharmacy records, microfiches, radiographs, and correspondence. Only members of the trial research team and the trial monitor will have direct access to the source data (i.e. hospital and pharmacy records) and trial documentation, which will be available to internal and external auditors if required. Access to the final data set will remain with the CI.

#### Plans for communicating important protocol amendments to relevant parties (e.g. trial participants, ethical committees) {25}

Any significant changes to the protocol outlined above (e.g. study objectives, study design, patient population, sample sizes, study procedures, or significant administrative aspects) will be written into a formal substantial amendment and approved by the ethics committee before implementation. New information that affects the risk/benefit assessment that results in changes to the consent form will require participants to be re-consented.

#### Dissemination plans {31a}

The study’s findings will be reported and disseminated at scientific conference presentations and in peer-reviewed journals and through engagement with medical providers, charities and community organisations, media, and the government. In particular, we will promote the outcomes of this study through lay-audience presentations, social media, and written feedback to patient support groups, as well as internal reports and articles on our lab webpages, which are publicly accessible.

## Discussion

Young children with SCA often have cognitive difficulties, specifically involving slowed processing speed [96–98]. These processing speed difficulties appear to be related to the brain’s deep white matter vulnerability to hypoxic-ischaemic injury [22]. Oxygen saturation often falls during sleep, especially if there is airway obstruction associated with the size of the adenoids in the nose as well as the tonsils, clinically detected as snoring [99]. There is preliminary evidence that suggests that children with SCA often have SDB associated with deficits in processing speed which early intervention could ameliorate [31]. However, the evidence base that widely used interventions, such as adenotonsillectomy and CPAP, to improve cognitive function is currently not strong, and consensus on treatment strategies has not yet been achieved [35, 38–40]. Montelukast is a safe, well-tolerated anti-inflammatory agent that mediates leukotrienes, which are key inflammatory mediators in the respiratory system. Several double-blind RCTs have demonstrated efficacy compared to placebo in the treatment of asthma in young children, and it reduces the size of the adenoids in children who do not have SCA [55–58]. However, we do not yet know whether montelukast would reduce adenoid size and improve processing speed in young children with SCA.

The SMILES trial aims to recruit 200 paediatric patients with SCA and SDB aged 3–7.99 years to assess the effect of montelukast on processing speed. Patients will be randomised to either montelukast or placebo for 12 weeks. Processing speed influences both intelligence and creativity, and these domains have an impact on school performance [100]. They often have reduced academic attainment compared to siblings and peers. Additional secondary outcomes will assess whether montelukast reduces adenoidal size and improves white matter integrity and executive function whilst seeing associated reduced respiratory and pain symptoms and improved sleep quality.

Potential challenges for the SMILES trial include recruiting a sufficient number of children into the study. The trial is being conducted within the context of the COVID-19 pandemic. Although vaccinations have begun, participants may be wary about taking part in research. As noted in our statistical analyses section, we can still answer important questions about adenoidal size, even with a reduced sample. Additionally, our research coordinator has kept in regular contact with many families, and they have indicated that if we begin the study, they would be willing to participate. Patients are also steadily referred to all collaborating centres. The research team has experience recruiting families (recently recruited 100 preschoolers); therefore, we feel the numbers proposed will still be achievable. In addition to recruitment challenges, caregivers may decline to complete all measures and tests. As such, we will prioritise our primary outcomes (i.e. processing speed) for patients and montelukast adherence monitoring for caregivers.

Hydroxyurea also improves oxygen saturation and is recommended for young children with SCA [101]. Families from the UK have expressed some concerns, so they may be reluctant to start this drug in asymptomatic young children. However, children with severe SCA may have been prescribed hydroxyurea, so we will account for this treatment in analyses. Cooperation in the MRI scanner may be an issue for younger children. The research team has experience applying neurophysiological methods with young children and will use these skills to adapt to an MRI ‘mock-scanner’ training regime. To maintain blinding, we will use a placebo and maintain the blind assessment of cognitive, oximetry, and imaging endpoints as we have done in previous studies of devices for SDB treatment.

Previous research indicates that interventions targeting hypoxic exposure may improve processing speed in young children with SCA [31, 44]. Thus, the SMILES trial will obtain data to determine if montelukast improves processing speed in young children with SCA and SDB. Findings from this study will also increase our understanding of whether montelukast is an effective treatment for young children with SCA. More broadly, data from this study may be utilised within the context of reducing emergency healthcare utilisation and improving quality of life for children with SCA.

## Trial status

SMILES protocol version 1.6, May 6, 2020. Recruitment will begin in April 2021 and is expected to be completed by September 2022.

## Abbreviations

BRIEF-2: Behavioral rating inventory of executive function
C-ACT: Childhood asthma control test
CBF: Cerebral blood flow
CI: Chief investigator
CEFIS: COVID-19 exposure and family impact survey
COVID-19: Coronavirus disease (SARS-CoV-2)
CPAP: Continuous positive airway pressure
CRF: Case report form
CSHQ: Children’s sleep habits questionnaire
DMC/DMSC: Data monitoring committee / data monitoring and safety committee
DTI: Diffusion tensor imaging
ESS: Epworth sleepiness scale
EudraCT: European clinical trials database
FLAIR: Fluid-attenuated inversion recovery
GOSH: Great Ormond street hospital
GSTH: Guys and St. Thomas hospital
NIMP: Impact project management
MAQ: Medical adherence questionnaire
MPM: Multiparametric map sequence
MRI: Magnetic resonance imaging
NHS: National health service
PedsQL: Pediatric quality of life
PSQ: Pediatric sleep questionnaire
PI: Principal investigator
R&D: NHS trust R&D department
RBC: Red blood cell
RCT: Randomised controlled trial
rsFMRI: Resting-state fMRI sequence
SCA: Sickle cell anaemia
SCD: Sickle cell disease
SCI: Silent cerebral infarct
SDB: Sleep-disordered breathing
SMILES: **S**tudy of montelukast in children with sickle cell disease
SO_2_: Oxygen saturation
SOP: Standard operating procedure
SCORE-15: Systemic clinical outcome and routine evaluation
TMF: Trial master file
TRUST: T2-relaxation-under-spin-tagging
UCL: University college London
WISC-V: Wechsler intelligence scale for children fifth edition
WPPSI-IV: Wechsler preschool & primary scale of intelligence fourth edition
